## Abstract

**Background:**

Perioperative brain protection in older patients has been the focus of research recently; meanwhile, exploring the relationship between regional cerebral oxygen saturation (rSO_2_) and brain function in the perioperative period has been an emerging and challenging area—the difficulties related to the real-time monitoring of rSO_2_ and the choice of feasible interventions. As an advanced instrument for intraoperative rSO_2_ monitoring, the clinical application of near-infrared spectrum (NIRS) cerebral oxygen monitoring has gradually increased in popularity and is being recognized for its beneficial clinical outcomes in patients undergoing cardiac and noncardiac surgery. In addition, although sufficient evidence to support this hypothesis is still lacking, the effect of permissive hypercapnia (PHC) on rSO_2_ has expanded from basic research to clinical exploration. Therefore, monitoring intraoperative rSO_2_ in older patients with NIRS technology and exploring possible interventions that may change rSO_2_ and even improve postoperative cognitive performance is significant and clinically valuable.

**Methods:**

This study is a single-center randomized controlled trial (RCT). 76 older patients are enrolled as subjects. Patients who meet the screening criteria will be randomly assigned 1:1 to the control and intervention groups. PHC-based mechanical ventilation will be regarded as an intervention. The primary outcome is the absolute change in the percent change in rSO_2_ from baseline to the completion of surgery in the intervention and control groups. Secondary outcomes mainly include observations of intraoperative cerebral oxygenation and metabolism, markers of brain injury, and assessments of patients' cognitive function using scale through postoperative follow-up.

**Discussion:**

The findings of this RCT will reveal the effect of PHC on intraoperative rSO_2_ in older patients with nonacute fragile brain function (NFBF) and the approximate trends over time, and differences in postoperative cognitive function outcomes. We anticipate that the trial results will inform clinical policy decision-makers in clinical practice, enhance the management of intraoperative cerebral oxygen monitoring in older patients with comorbid NFBF, and provide guidance for clinical brain protection and improved postoperative cognitive function outcomes.

**Trial registration:**

ChiCTR, ChiCTR2200062093, Registered 9/15/2022.

## Background

Permissive hypercapnia (PHC), a lung-protective ventilation strategy, can avoid lung injury caused by a high tidal volume and hyperventilation as much as possible and allows a moderate increase in PaCO_2_ and a certain degree of acidemia when maintaining appropriate gas exchange and reducing ventilation pressure is not compatible. Extensive clinical experience has been accumulated on the application of PHC during the treatment of mechanical ventilation-induced acute lung injury and acute respiratory distress syndrome (ARDS) in ICU patients, proving that PHC exerts anti-inflammatory and protective effects on multiple organs [1]. Importantly, as an add-on effect of the lung-protective ventilation strategy, the clinical application of PHC is more correlated than causally related to the purpose of treatment, and the direct lung-protective effect of small tidal volumes and low ventilation pressures is the central focus of the study, with PHC presented more as an incidental outcome and blood gas monitoring indicator. In other words, the current research paradigm mainly attributes the protective effect of these ventilation strategies to the reduction of lung tension alone, whereas hypercapnia is only intended to achieve this goal, and the relative independent clinical significance and acceptability of PHC itself remain widely questioned. However, in recent years, the positive effect of hypercapnia on basic research and perioperative clinical management has received increasing attention.

The traditional view is that a normal or low PaCO_2_ should be maintained during surgery because hypercapnia may lead to tachycardia and elevated blood pressure during the operation, resulting in increased oxygen consumption and a series of adverse perioperative effects. However, an increasing number of preclinical and clinical studies have recently supported the multiorgan-protective effects of hypercapnia, and the protective effect on the brain is a hot topic among these studies [2–6]. PHC can mediate the complex regulation of brain homeostasis in many aspects, such as brain microcirculation and the oxygen supply–demand balance [7–9], brain activity and metabolism [10–12], secretion of excitatory amino acids and neurotransmitters [13], free radical-induced damage [14, 15], the inflammatory response [16, 17], and apoptosis mechanism [6], thus realizing the positive protective effect on brain function. In addition to the extensive basic experimental evidence, several clinical trials have likewise documented the potential for PHC. One study found that the incidence of hypocapnia in patients during general anesthesia reaches 66% and that the postoperative length of hospitalization, morbidity, and mortality is increased in patients with low PETCO_2_ levels during anesthetic management [18]. Moreover, Way and Hill provided evidence that mild hypercapnia (PETCO_2_ values of approximately 40 mmHg or higher) improves the patient prognosis compared to mild hyperventilation and hypocapnia and is associated with a reduced incidence of postoperative complications [19], implying that mild hypercapnia is beneficial and should be accepted as a routine standard of care.

Among these mechanisms of brain protection, maintaining normal brain oxygenation is one of the most critical factors in ensuring normal brain function. However, as a therapeutic ventilation strategy, any beneficial or detrimental effect of PHC on rSO_2_ in patients undergoing major surgery has not been adequately determined. In previous animal model studies, carbon dioxide was an effective vasodilator, particularly in the cerebral vasculature, with a high sensitivity to improve cerebral blood flow (CBF) [20–22]. The definitive neuroprotective mechanisms of mild hypercapnia are still elusive but are presumably associated with increased CBF, enhanced oxygen delivery, and improved cerebral glucose utilization and oxidative metabolism [23, 24]; moreover, mild hypercapnia may activate adenosine triphosphate-sensitive potassium channels to maintain regular neuronal activity during cerebral ischemic events [13]. Furthermore, in a previous study of PHC applied to the management of clinical anesthesia, PHC increased rSO_2_ and reduced the incidence of cerebral oxygen desaturation events (CDE) in patients undergoing general anesthesia [25–27]. This finding further confirms the existence of potential mechanisms by which PHC directly or indirectly affects cerebral oxygenation.

In recent years, NIRS cerebral oximetry has provided a practical method for the continuous noninvasive measurement of rSO_2_. This method has been used in acute and critical care resuscitation, intensive care, and surgical applications with substantial supporting evidence [28–30]. Many studies have also shown that NIRS can be applied during resuscitation and cardiac surgery to effectively monitor and manage hypoxic events in the brain [31–34]. However, although timely intervention is required when certain absolute and relative brain oxygen saturation thresholds are reached [35], these thresholds have not yet been verified, and agreement on the timing and indications for interventions is lacking. A corresponding increase in rSO_2_ has been reported in patients undergoing major surgery with mild hypercapnia, but the exact temporal relationship between intraoperative rSO_2_ and mild hypercapnia is unclear [9].

Notably, Mutch et al. [36] confirmed that the duration and severity of intraoperative hypocapnia are independent risk factors for postoperative cognitive dysfunction (POCD), but researchers have not yet validated whether maintaining hypercapnia during anesthesia is effective at reducing the incidence and severity of POCD and whether it leads to unforeseen adverse events in rigorous clinical trials. POCD is a common neurological complication occurring after anesthesia and surgery and is a recognized clinical phenomenon. In 1955, Bedford described it in the *Lancet* as an adverse effect of anesthesia on the brain of older individuals [37]. POCD is a transient interference of external factors (general anesthesia/surgery, etc.) on the nervous system, often with transient and reversible clinical characteristics. However, some patients may also suffer long-term cognitive impairment. It occurs in patients of all ages but is more common in older patients. The age-related decline of basic cognitive function, neurodegenerative changes, and higher incidence of cardiovascular and cerebrovascular diseases in older patients may be critical factors of age-orientation. Its main clinical manifestations are poor memory, comprehension, and attention after surgery and general anesthesia, which seriously affect the quality of life of patients undergoing surgery, prolong the length of hospital stay and even impose severe mental pressure and an economic burden on families and society [38, 39]. In addition, in recent years, many relevant studies have emerged describing the effect of rSO_2_ on postoperative cognitive outcomes, but the results of these studies are highly controversial.

On the one hand, many studies show that rSO_2_ is closely related to postoperative cognitive impairment and can even be used as an essential predictor of POCD [40–42]; on the other hand, the recent mainstream opinion based on clinical studies and meta-analyses seems to favor the lack of a significant correlation between intraoperative rSO_2_ and POCD [43–45]. However, patients with underlying brain diseases tend to have a worse basic cognitive function status and ability to self-regulate regional CBF and microenvironment homeostasis. Based on this premise, some issues must be reexamined: is the effect of rSO_2_ regulation on postoperative cognitive outcomes more clinically significant? Is the regulation of rSO_2_ one of the primary mechanisms by which PHC protects the brain protection? Is there a potential chain for the following relationship:* "PHC → improves cerebral oxygenation function → improves postoperative cognition"*? The answers to all these questions are inconclusive; thus, a clinical inquiry is vital for practice. Therefore, in selecting trial subjects, NFBF was considered the basic inclusion criterion according to the "*Guidelines for the management of perioperative anesthesia in older patients in China*" [46]. Fragile brain function without definite attack and corresponding clinical symptoms within nearly three months are defined as "non-acute fragile brain function" [*Cerebral Hemorrhage, Cerebral Infarction, Transient Ischemic Attack (TIA), Cerebrovascular Stenosis, Parkinson's Disease (PD), Long-term Headache and Dizziness*]. The qualification of "fragile brain function" and "nonacute" not only satisfies the screening of specific populations with more experimental significance but also ensures the safety and ethical guidelines of the trial as much as possible.

In addition, PETCO_2_ is closely related to PaCO_2_. Continuous noninvasive end-expiratory carbon dioxide monitoring has been used as a reliable indicator to evaluate PaCO_2_ in perioperative mechanically ventilated patients. During mechanical ventilation during general anesthesia, a high PETCO_2_ can be achieved by adjusting the respiratory rate or specified tidal volume, which makes permissible hypercapnia feasible and easy to implement in the management of general anesthesia.

In addition, laparoscopic surgery has become very convenient for older patients with colorectal cancer in recent years. However, CO_2_ pneumoperitoneum during laparoscopic surgery may affect the nervous system of patients and lead to postoperative cognitive dysfunction. In a prospective clinical study of 22 adult women, Liu et al. found that laparoscopic surgery (pneumoperitoneum pressure of 15 mmHg) significantly reduced the Mini-mental State Examination (MMSE) scores and increased the serum S-100β protein level at 1, 6, 12, 24, and 72 h after surgery compared with traditional open surgery [47]. Two potential explanations have been proposed: hypercapnia caused by CO_2_ pneumoperitoneum and the adverse effect of pneumoperitoneum pressure. Admittedly, some conventional views suggest that hypercapnia negatively affects postoperative cognitive outcomes. The theoretical basis of brain edema, high intracranial pressure, central nervous system ischemia, and hypoxia due to the subsequent dilatation of the cerebrovasculature caused by hypercapnia of the CO_2_ pneumoperitoneum seems to provide possible support for this hypothesis. However, the specified pathophysiological mechanism has mainly been explored using basic research, and we must be clear that the situation may be different when the scale of hypercapnia is further refined to permissive hypercapnia. By adjusting the ventilation strategy, the patient is eased into a treatment-acceptable acidic environment, and relatively stable conditions are maintained during the operation by PETCO_2_ and intermittent blood gas measurements. The effect on the patient's body differs substantially from animal models or cellular and molecular models with a rapid/highly acidic environment. This hypothesis is strongly supported by several previous preclinical and clinical studies on the hazards of hypercapnia and the beneficial outcomes of permissive hypercapnia [5, 6, 48–50].

Moreover, pneumoperitoneum pressure is another factor that must not be ignored, and the lower the pneumoperitoneum pressure is, the less of an effect on the body will be observed. Studies have shown that pneumoperitoneum pressure aggravates neuroinflammation and cognitive impairment induced by surgery in aged mice [51]. However, laparoscopic surgery was selected as the surgical method in the present study, indicating that laparoscopic pneumoperitoneum factors were set as control variables, and the independent effects on cerebral oxygen and postoperative cognitive function were unable to be further explored. However, the selection of basic research methods, based on their wide use and practical significance, will undoubtedly further amplify the external effects of the final research conclusions and further improve the ethical practicality.

In summary, when the three key factors of "older patients," "fragile brain function," and "CO_2_ pneumoperitoneum and laparoscopic surgery" are linked together, the protection of the perioperative cognitive function of patients must receive increasing attention. Notably, the change and adjustment of CO_2_ pneumoperitoneum pressure are extremely limited due to the essential requirement of a clear operative field for delicate surgical operations. However, it seems to be a pioneering prospect from the perspective of hypercapnia. First, although permissive hypercapnia was the intervention used in our study, in combination with clinical practice, mild hypercapnia itself is difficult to avoid in major laparoscopic surgery, and extreme ventilation parameter settings (high respiratory rate/high tidal volume) are often required to force normal conditions, which may exert adverse effects. Therefore, our intervention is different from that used in most other RCTs. We evaluated the advantages and disadvantages of both in terms of justifying their existence and acceptability in terms of medical factors, combined with the adverse effects (lung tissue traction injury, airway pressure damage, hyperventilation, respiratory muscle fatigue, tachycardia, etc.) of the forced manual setting of ventilation parameters to achieve a normal blood pH. Previous preclinical and clinical studies of the effects of hypercapnia on the central nervous system and postoperative cognitive function have largely produced negative results; however, further explorations are needed to determine whether this problem can be further improved when hypercapnia is converted to a more precise state of permissive hypercapnia.

Therefore, we will conduct a prospective, single-blind RCT. Laparoscopic colorectal surgery is used as the surgical method and older patients with NFBF are defined according to the "*Guidelines for the management of perioperative anesthesia in older patients in China*" [46], which are the main inclusion criteria used to explore our established hypothesis that the PHC group (H) will exhibit improved brain oxygenation and increased rSO_2_ compared with the target normal group (N) (Table 1). In addition, as a secondary objective, we will evaluate whether PHC affects postoperative cognitive outcomes and further verify the existence of the potential mechanism of "*PHC → improves cerebral oxygenation → improves postoperative cognition*."

**Table 1 Tab1:** Definition and classification of NFBF

Classification of NFBF	Definition of NFBF
Cerebral haemorrhage	Non-traumatic haemorrhage is caused by rupture of blood vessels in the brain parenchyma, accounting for 20–30% of all strokes
Cerebral infarction	Also known as *cerebral ischemic stroke*, it is an ischemic necrosis or softening of limited brain tissue caused by ischemia and hypoxia due to impaired blood supply to the brain (*Cerebral thrombosis, lacunar infarction and cerebral embolism*)
Transient ischemic attack (TIA)	A transient, limited cerebral deficit or retinal dysfunction caused by a cerebrovascular lesion, with clinical symptoms generally lasting 10–20 min, mostly resolving within 1 h and up to 24 h, with no residual neurological deficit symptoms and no responsible lesions on structural imaging (CT, MRI)
Craniocerebral vascular stenosis	Several factors cause the narrowing of blood vessels in the brain, reducing the amount of blood flow and oxygen supply, and causing localized ischemia and hypoxia in brain tissue, resulting in a series of clinical symptoms (*congenital cerebral stenosis/spastic cerebral stenosis*)
Alzheimer's disease (AD)^a^ ***(exclusion)***	A neurodegenerative disease whose various pathophysiological aspects are still under investigation, characterized by a progressive decline in cognitive function and specific types of neuronal and synaptic loss, the most recognized pathological events are amyloid plaques and neurofibrillary tangles
Parkinson's disease (PD)	A common and complex neurological disorder whose core is a neurodegenerative disease with early prominent death of dopaminergic neurons in the substantia nigra pars compacta (SNpc)
Chronic headache/ Chronic dizziness	Information was obtained from all inquiries during the preoperative visit and hospitalization

Fragile brain function without definite attack and corresponding clinical symptoms within nearly three months are defined as "non-acute fragile brain function"; AD^a^ is often accompanied by severe preoperative cognitive dysfunction, which does not meet the inclusion criteria

## Methods

### Study design, setting and participants

Between October 2022 and July 2023, we plan to conduct an RCT at Shengjing Hospital of China Medical University (Shenyang, China), a university teaching, higher education, large general hospital. The trial period is expected to be 10 months, during which patient recruitment, intervention implementation, and postoperative follow-up will be conducted in an orderly manner according to the actual situation. The final results are expected to be reported in October 2023. Participants will be screened from the patients proposed for elective laparoscopic colorectal surgery in the gastrointestinal surgery department of the hospital. Patients who are eligible for elective major surgery are identified after a preoperative evaluation and receipt of written informed consent before the patient's surgery date. Patients who meet the screening criteria will be randomly assigned 1:1 to the control group (Conventional ventilation group parameters: Tidal volume10 ~ 12 mL/kg, Respiratory rate 14 ~ 16 bpm, Suction/Respiration ratio 1:2, PaCO_2_ 35 ~ 45 mmHg, PEEP 0 cmH_2_O, FiO_2_ 40%) and the intervention group (Permissive hypercapnia group parameters: Tidal volume 6 ~ 8 mL/kg, Respiratory rate 12 ~ 14 bpm, Suction/Respiration ratio 1:2, PaCO_2_ 45 ~ 55 mmHg, pH > . 7.2, PEEP 0 cmH_2_O, FiO_2_ 40%), and 38 patients will be included in each group. Baseline preoperative rSO_2_ values will be recorded, and real-time intraoperative rSO_2_ monitoring will be performed by investigators who are not providing the clinical intervention. In addition, patients will be followed up postoperatively with MMSE scale to assess early postoperative cognitive function. The patients with postoperative MMSE scores ≤ 23 and a decrease of more than 2 points from the baseline value were defined as delayed neurocognitive recovery (DNR). It should be noted that the follow-up personnel have received standardized training in advance, to ensure that the survey scale can be used scientifically and correctly (Fig. 1).

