
### Inclusion and exclusion criteria for the trial

#### Inclusion criteria

ASA status I-III;Age ≥ 65 years;BMI 18–28 kg/m^2^;Preoperative MMSE score ≥ 23 points;Conscious and able to think independently;Planned laparoscopic colorectal cancer surgery, no contraindication to surgery;Nonacute fragile brain function (*History of Cerebral Hemorrhage, Cerebral Infarction, TIA, Cerebrovascular Stenosis, PD, Long-term Headache and Dizziness, and no attack or corresponding clinical symptoms within three months*);Consent to participate in the trial.

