#### Secondary endpoints

Intraoperative T_1_, T_2_, T_3_, and T_4_ cerebral oxygen metabolism-related indexes (*rSO*_*2*_*, Da-jvO*_*2*_*ml/L, CERO*_*2*_*%*);Incidence of CDE (≥ *20% reduction in cerebral oxygen saturation relative to baseline or absolute rSO*_*2*_ ≤ *55%*);MMSE scores 1d before and 1, 3, and 7d after surgery and the incidence of DNR;1d preoperatively (baseline) and 1d postoperatively: serum neuron-specific enolase (NSE) and interleukin-6 (IL-6) levels;Time to awaken from anesthesia;Postoperative admission rate to ICU;The all-cause mortality rate at 30 days postoperatively (*follow-up*);Pulmonary complications after surgery (*bronchospasm, atelectasis, exacerbation of chronic lung disease, infection, prolonged mechanical ventilation, and respiratory failure*);Duration of the hospital stay;Presence of postoperative adverse events (*nausea, vomiting, hypotension, bradycardia, and excessive sedation*): ①A 20% reduction in systolic blood pressure relative to baseline or MAP < 65 mmHg is defined as a perioperative hypotensive event; ②Heart rate < 50 beats/min is defined as bradycardia; ③Level of sedation assessed using the Ramsay scale (*Level 1 awake*: the patient is anxious, restless or irritable; *Level 2 awake*: the patient is cooperative, well-oriented or quiet; *Level 3 awake*: the patient responds only to commands; *Level 4 sleep*: the patient is responsive to tapping between the eyebrows or strong vocal stimuli; *Level 5 sleep*: the patient is unresponsive to tapping between the eyebrows or strong verbal stimuli; *Level 6 sleep*: the patient does not respond to tapping between the eyebrows or strong verbal stimuli), where a Ramsay level ≥ 3 is defined as excessive sedation.

(**T**_**0**_: Immediately after entry, before any treatment **T**_**1**_: 15 min after tracheal intubation **T**_**2**_: 60 min after pneumoperitoneum **T**_**3**_: 120 min after pneumoperitoneum **T**_**4**_: suture completion, end of surgery).

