The MMSE is one of the most influential and popular international screening instruments for cognitive impairment, covering time, place orientation, immediate memory, attention, computation, short-term memory, language, and visuospatial structure skills. However, a capping and learning effect exists for the MMSE. The MMSE is insensitive to subtle changes in cognitive function that may occur after surgery. Thus, the MMSE is more suitable for preoperative screening in PND studies. The MoCA covers a broader range of cognitive domains than the MMSE, which makes it seems to be more accurate and sensitive than the MMSE for the determination of mild cognitive impairment. But our previous pilot study showed that the MoCA is too difficult and time-consuming to implement. Therefore, we will choose the MMSE as the assessment tool for postoperative cognitive function outcome (The patients with postoperative MMSE score ≤ 23 and a decrease of more than 2 points from the baseline value were defined as DNR). In addition, as a secondary outcome measure, we can accept the limitations of the MMSE.

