### Statistical analysis

Data will be analyzed using Statistical Package for Social Science 25.0 software. The Shapiro–Wilk test is used to test the normality of continuous variables, expressed as means and SDs if they are normally distributed and as medians and interquartile ranges if they are non-normally distributed. Baseline, Intraoperative, and postoperative indicators between the intervention and control groups are analyzed by t-tests, Mann–Whitney U test, chi-square test, continuous corrected chi-square test, or Fisher's exact test (Table 3). All primary and secondary outcomes analysis will be based on intention-to-treat (ITT) which means all patients who accept randomization will be included in the final statistical analysis, regardless of whether they received the intended intervention. We will also conduct per-protocol (PP) analysis for primary and secondary outcomes. ITT analysis usually attenuates differences between two groups, and PP analysis exaggerates differences between two groups. We will explore the consistency of ITT and PP analysis results and verify the results' reliability if they are consistent in the end. For the primary outcome, linear regression models will be used to generate unadjusted effect sizes with 95% confidence intervals. Preoperative baseline and intraoperative data are also included in the linear model to generate adjusted effect sizes and 95% confidence intervals. The analysis of repeated measures (rSO_2_, Da-jvO_2_, CERO_2_) will be performed using generalized estimating equations (GEE), with patient code (ID) as the within-subject variable, time as the between-subject variable, and rSO_2_, Da-jvO_2_, and CERO_2_ as the dependent variable. The ACE-R scores of the intervention and control groups will also be analyzed by GEE. What we need to be clear is that we will not adjust for multiple comparisons of secondary outcomes at numerous measurement time points, and we will focus on the separate effects of intervention because these results are exploratory. The incidence of CDE and DNR between the intervention and control group will be analyzed by the chi-square test, continuous corrected chi-square test, or Fisher's exact test. The serum NSE and IL-6 concentrations between the intervention and control groups are analyzed by covariance (ANCOVA) analysis, and the least-squares mean (LSM) difference and 95% CI will be estimated. Postoperative adverse events will be analyzed using the safety analysis set, which refers to patients who received at least one intervention in their group. Postoperative adverse events are categorical data, and the chi-square test, continuous corrected chi-square test, or Fisher's exact test will be used for statistical analysis.

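### The two-part DNR rule needs a fall of 3 MMSE points from low-baseline patients but up to 7 from high-baseline patients, and the planned DNR test ignores baseline MMSE

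*Protocol article*

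**What the plan says.** The rule appears twice in the protocol article with the same meaning. Study design, setting and participants gives it as "postoperative MMSE scores ≤ 23 and a decrease of more than 2 points from the baseline value"; Measurement of PNDs repeats it as "postoperative MMSE score ≤ 23 and a decrease of more than 2 points from the baseline value were defined as DNR". The Inclusion criteria admit patients with "Preoperative MMSE score ≥ 23 points".

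Secondary endpoints lists "MMSE scores 1d before and 1, 3, and 7d after surgery and the incidence of DNR", so the raw scores are an outcome as well as the derived category. For the category, Statistical analysis states: "The incidence of CDE and DNR between the intervention and control group will be analyzed by the chi-square test", with the continuity-corrected chi-square or Fisher's exact test as alternatives. No baseline term is named for this comparison.

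Measurement of PNDs concedes that "a capping and learning effect exists for the MMSE" and that "The MMSE is insensitive to subtle changes in cognitive function that may occur after surgery", and accepts these limits because the outcome is secondary. Those remarks concern the scale. Nothing explains why an absolute cut-off is added to the decline criterion, or notes that the two together ask for different falls from different patients.

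**The concern.** DNR is meant to mark cognitive worsening after surgery. Because the two parts are joined by a conjunction, the binding part changes with the starting score. For low baselines the decline part decides. For high baselines the cut-off decides, and it asks for more than a 3-point fall. A patient who goes from 26 to 23 (3 points) is a case; one who goes from 30 to 24 (6 points) is not. A patient who enters at exactly 23 meets the cut-off before surgery, so for that patient the cut-off does not mark a new state.

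DNR is the only categorical cognitive outcome, and Anticipated results predicts that permissive hypercapnia will reduce it. If part of the decline is not counted and baseline explains much of who becomes a case, a comparison of 38 against 38 that ignores baseline gives up information the trial already collects.

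**Working it through.** **Inputs from the protocol.** Postoperative cut-off ≤ 23; fall of more than 2 points; entry at ≥ 23; 38 patients per arm.

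**Inputs assumed.** The MMSE takes whole numbers up to 30 (a property of the scale that the article does not print). The protocol gives neither the baseline distribution nor the expected fall, so both are varied. It states no DNR rate or power, so there is no figure of its own to reproduce.

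**Step 1: fall needed at each baseline.** A fall of more than 2 points means at least 3. Reaching 23 or below needs a fall of at least baseline − 23. Together: fall needed = max(3, baseline − 23).

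| Baseline | Fall needed | Falls above 2 points not counted |
|---|---|---|
| 23 to 26 | 3 | none |
| 27 | 4 | 3 |
| 28 | 5 | 3, 4 |
| 29 | 6 | 3, 4, 5 |
| 30 | 7 | 3, 4, 5, 6 |

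This step is exact, given the 30-point maximum.

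**Step 2: share of decliners missed, central case.** Assume one postoperative assessment; baseline normal with mean 27 and SD 2, rounded and restricted to 23 to 30; fall normal with mean 2 and SD 2, rounded, with the same distribution at every baseline.

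- Baseline shares: 23 to 26, 0.4106; 27, 0.2083; 28, 0.1843; 29, 0.1277; 30, 0.0692.
- Probability of a fall of at least 3, 4, 5, 6, 7 points: 0.4013, 0.2266, 0.1056, 0.0401, 0.0122.
- P(DNR) = 0.4106 × 0.4013 + 0.2083 × 0.2266 + 0.1843 × 0.1056 + 0.1277 × 0.0401 + 0.0692 × 0.0122 = 0.237.
- Missed share = 1 − 0.237/0.4013 = 41%.
- DNR rate at baseline 26 or below: 40%. At 28 or above: (0.0195 + 0.0051 + 0.0008)/0.3812 = 7%, with identical falls.

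**Step 3: range.** The same calculation, with both SDs kept at 2:

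| Baseline mean | Mean fall 1 | Mean fall 2 | Mean fall 3 |
|---|---|---|---|
| 25 | 17% | 15% | 13% |
| 26 | 30% | 27% | 22% |
| 27 | 45% | 41% | 35% |
| 28 | 61% | 56% | 49% |

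A wider grid (baseline means 25 to 29, baseline SD 1.5 or 2, mean fall 1 or 2, fall SD 2 or 3) runs from 7% to 83%.

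**Step 4: what the analysis change buys.** With 38 per arm, baseline mean 27 and an assumed treatment effect of 1.5 points, simulated power for the two-part rule rose from about 50% unadjusted to about 56% with baseline MMSE in the model. The decline-only outcome had about 73%. Repeating this with the control arm's mean fall set at 2 and then 3 points (3,000 trials each) gave 46% and 56% unadjusted (chi-square), 50% and 63% adjusted (logistic likelihood-ratio test), and 67% and 73% for decline-only. With no treatment effect (mean fall 2), rejection rates at the 5% level were 5.0% for chi-square, 2.7% for Fisher and 6.0% for the adjusted test. The adjusted test is thus slightly liberal at this size, so part of its small gain comes from that.

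**The case against.** The rule can be defended as a deliberate choice. It is stated consistently, and requiring both a clear decline and a low final score favours specificity on a scale with ceiling, learning and retest effects. A decline-only rule would count 30 to 27 as DNR, and the protocol gives no ground for calling every such fall true impairment. This stands: it is a reason to keep the two-part rule and add to it, not to replace it.

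Three stronger readings are tempting, and the documents do not support them.

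- A reader might infer that DNR mainly records who entered with a low score. Every case still needs a postoperative fall of at least 3 points, including a patient who enters at 23. Strong dependence on baseline is as far as the evidence goes.
- A reader might infer a biased comparison. Randomisation keeps the unadjusted test valid, and the null rejection rates above show no inflation for it. In a simulation under the central assumptions, chance imbalance in mean baseline MMSE explained only about 12% of the variance in the between-arm DNR difference.
- A reader might infer that most or many decliners are certainly lost. Nobody with a baseline of 23 to 26 is missed. In an older population with prior cerebrovascular disease or Parkinson's disease, admitted from 23, a low baseline mean is plausible and the loss would then be small.

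It is also fair that the raw MMSE scores are a separate endpoint, so declines from high baselines are recorded, and that the Discussion says the trial was not designed to quantify the cognitive effect. The mitigation is partial: Statistical analysis assigns the repeated-measures model to ACE-R scores, an instrument named nowhere else in the article, and so names no such model for the MMSE.

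**Conclusion.** The point holds as a loss of sensitivity and precision in an exploratory secondary endpoint. The fall needed, 3 points at baselines 23 to 26 rising to 7 at 30, follows from the protocol's own rule and entry criterion plus the 30-point maximum. That falls of 3 to 6 points at baselines 27 to 30 can go uncounted is equally certain.

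How often this happens is not. About 13% to 61% of decliners would be missed for assumed baseline means of 25 to 28 and mean falls of 1 to 3 points, both SDs 2. That range rests on normal shapes, one assessment, and falls unrelated to baseline. The gain from adjustment is modest. The larger gain from decline-only counting depends on the assumed 1.5-point effect applying equally across baselines. The primary outcome is untouched.

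**What to change.** In Statistical analysis:

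1. Compare DNR between arms with a model that includes the MMSE score from one day before surgery (for example, logistic regression), in place of the unadjusted chi-square or Fisher test alone. The unadjusted test can stay as a supporting result. With few events, a penalised or exact version would guard against the slight liberality seen above.
2. Prespecify a decline-only analysis, a fall of more than 2 points at every baseline, reported alongside the two-part rule. The fall needed is then 3 points for everyone.

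The definition in Study design and in Measurement of PNDs can remain, ideally with a sentence saying why the cut-off is there and that it asks for larger falls from higher scorers.

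The cost is slightly more analysis and a change of wording. All the scores are already collected. The decline-only rate will be higher, is less comparable with studies that use an absolute cut-off, and may include some retest noise, which is why both versions should be shown.
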